## 8.2 Randomisation, blinding and treatment allocation

The allocation scheme will be created by an independent researcher with a computerized random number generator (Random Allocation Software) with block sizes of 6, 8, 10, and 12 and at an allocation ratio 1:1. Participants will be randomized into two groups: ZeroPhobia or

waitlist condition. Due to the nature of the study, double blinding for treatment allocation is not possible.

### 8.3 Study procedures

Advertisements with a call to participate in a VR mobile app study for aviophobia and arachnophobia will be posted on several media outlets (Radio, TV), websites (e.g. Fonds Psychische Gezondheid, Angst Fobie en Dwangstichting, Google Adwords, Facebook), mental health institutes (e.g. Stichting Valk for Aviophobia) and in magazines (e.g. de Ingenieur). When a person is interested to participate in the study, s/he can use the URL of the website provided in the advertisement to be directed to the study homepage of ZeroPhobia. On this page, information about the study is provided, including eligibility criteria. If the person thinks s/he fulfills the inclusion criteria and is interested to participate in the study, s/he will be invited to click on a link ('aanmelden'), which will ask them to input their name and email. This information will be sent directly to our secure email inbox, so that we can provide the participants with further study information.

Our website is hosted on one of Vrije Universiteit's Faculty of Movement and Behavior Sciences (FGB) research webserver. This server is located in the server room on the VU campus. Access to this server and room is restricted to system administrators (TO3). Content, such as text, on the website are of the responsibility of the research team. Problems in terms of technical website functioning are the responsibility of TO3.

The website itself is only accessible via the HTTPS protocol and is secured by a SSL-certificate to encrypt all traffic between the web-browser and server. Other than webserver-logs necessary for the webserver, no information about the website visitors is stored on the server.

Information (name and email of the participant) will be received by the researcher, with which we will email more information about the study, specifically the consent form, the participant information letter, and the CMO brochure. In this email, we will ask that if they are still interested in participating after reading these materials, for them to use the provided link to a secure survey.

This survey will allow them to provide a physical mailing address, so hard copies of consent and informational materials can be mailed to them. Screening questions will also include items about age, Dutch fluency, whether or not they are currently receiving psychiatric services for their phobia, and either the FAS or FSQ (duration of 15 minutes). This screener is given prior to official consent in order to save ineligible participants time and prevent unnecessary baseline data from being collected. If participants do not meet inclusion criteria, an automatic email will be sent to them notifying them of their exclusion and the reasoning of such. If participants are

eligible, a trigger email will be sent to the researchers to let us know they meet criteria to participate. This screening information will not be used for any other purposes other than to determine inclusion and exclusion; all screening survey responses will be deleted after participant's eligibility has been determined.

If eligible, according to the basic screener, and still interested, the research assistant will send the patient information letter and informed consent form to their home address with a return envelope. If necessary, the researcher will remind them by email to complete the informed consent (2 reminders in total, second being a phone call). The informed consent form will be sent to each participant. The participant will be instructed to sign the consent form and mail it back to us. Once received, we will sign the consent form as well and then make a copy of the consent form. This copy will be mailed back to the participant to keep for their own records.

Upon receiving informed consent, the researcher will send a second survey link to participants via email to complete a baseline measurement. In this baseline measurement, demographic variables (gender, level of education, marital level), FAM (aviophobia) or SPQ (arachnophobia), PHQ, BAI, WSQ, and IRI will be measured (duration of 20 minutes).

If necessary, the researcher will remind them by email to complete the baseline measurement (2 reminders in total, second being a phone call). After the baseline has been completed, participants will be randomized by an independent researcher. The research assistant will notify the participant of which condition they have been randomized to, either the intervention condition or the waitlist condition.

If in the intervention condition, the research assistant will send the VR glasses to the participant by postal delivery, along with usage instructions. The research assistant will email the participant with instructions on how to download the ZeroPhobia app to his/her smartphone. The app is locked with an individual code which will be given to the participant at the start of the intervention. Participants can then begin the ZeroPhobia intervention which they can follow for 6 weeks (5-20 minutes per week, in addition to VRET from module/week 3 onward, which we recommend 10 minutes a day of practice with). When practicing in VRET, participants are asked to fill in one question about their anxiety level before, during, and after VRET (duration: 5 seconds). Participants can follow the intervention at their own pace. Participants will receive weekly automatic reminder emails to begin or continue the intervention from the research assistant. If needed (e.g., with a question about how to use ZeroPhobia or in the unlikely case of distress), participants will be invited to contact the research assistant.

If in the wait-list condition, the participant will be informed that after a six week pause and the completion of a post-test assessment, they can begin the ZeroPhobia program. The wait-list group will undergo the same program procedure as those in the treatment condition. Participants of both conditions will begin the program on the first working Monday after

completing the baseline and being randomized to a condition, meaning participants of both groups will have different start and end times. Both groups will have the same duration of each section, however (see flowchart).

The aforementioned post-test (occurring after 6 weeks of either intervention or pause, or after the completion of module six in the intervention group (for those participants who choose to work through the ZeroPhobia program faster) consists of the FAS and FAM (aviophobia) or FSQ and SPQ, (arachnophobia), PHQ, BAI, IPQ, SUS, CEQ and NEQ, questions regarding whether they received professional treatment during this time, and questions about flight usage (duration: 25 minutes). Two reminders will be given across two weeks to fill in post-test, the first being an e-mail and the second a phone call.

Those who were randomized to the intervention condition will also receive 3- and 12-month follow-up questionnaires. These surveys will include the FAS and FAM (aviophobia) or FSQ and SPQ (arachnophobia), PHQ, BAI, questions about receiving professional treatment for their phobia, and flight usage questions (duration: 20 minutes). Two reminders will be given across two weeks to fill in follow-up questionnaires, the first being an e-mail and the second a phone call. All assessments are programmed with Survalyzer software. For an overview of measurements, see Table 1. If desired, general information about the outcomes of the study will be sent to the participant after completion of the study.

*Table 1: Overview of measures*

| Measures     |                                                                               |          |                |                         |
|--------------|-------------------------------------------------------------------------------|----------|----------------|-------------------------|
|              | Aim                                                                           | Baseline | Post-test (6w) | Follow-up (3, 12 month) |
| Demographics | To determine characteristics of sample                                        | x        |                |                         |
| FAS or FSQ   | To determine symptoms of aviophobia/arachnophobia and treatment effectiveness | x        | X              | x                       |
| FAM or SPQ   | To determine symptoms of aviophobia/arachnophobia and treatment effectiveness | x        | x              | x                       |
| BAI          | To determine symptoms of anxiety and treatment effectiveness                  | x        | x              | x                       |

|                                                   |                                                                                     |   |   |   |
|---------------------------------------------------|-------------------------------------------------------------------------------------|---|---|---|
| PHQ                                               | To determine symptoms of depression and treatment effects                           | x | x | x |
| SUS                                               | To determine program's user-friendliness                                            |   | x |   |
| CEQ                                               | To determine program's user-friendliness                                            | x |   |   |
| NEQ                                               | To determine whether there are any negative effects of ZeroPhobia                   |   | x |   |
| IPQ                                               | VR experience                                                                       |   | x |   |
| IRI                                               | To determine influence of fantasizing ability on effectiveness of VRET              | x |   |   |
| WSQ                                               | To control for confounding variables                                                | x |   |   |
| Flight usage                                      | To determine effectiveness of treatment                                             | x | x | x |
| General flight anxiety questions                  | To further understand the type of flight anxiety a participant has                  | x |   |   |
| User-friendliness and realism questions           | To further understand the user experience of the ZeroPhobia app and VR environments |   | x |   |
| Professional treatment (medication and treatment) | To control for confounding variables                                                | x | x | x |

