**Intervention:** The intervention ZeroPhobia is 6-week self-help VRET for aviophobia and arachnophobia that is delivered through a smartphone application (app) in combination with rudimentary cardboard VR goggles. ZeroPhobia includes modules of psychoeducation, case examples, exposure through VR, cognitive techniques, monitoring of symptoms, and relapse prevention. Participants in the waitlist condition will be offered the intervention directly after post-test.

**Main study parameters/endpoints:** The main study parameters are the post-test differences in phobic anxiety symptoms between the experimental and control condition, and follow-up differences in anxiety symptoms between baseline and follow-up in the experimental condition.

**Nature and extent of the burden and risks associated with participation, benefit and group relatedness:** The burden of participation consists of completing online baseline questionnaires (15 minutes) and performing the intervention (6 modules lasting 5-20 minutes across 6 weeks and daily VR exposure practice from module/week 3 onwards, recommended 10 minutes daily). In addition, participants will be asked to complete an online post-intervention assessment immediately after completion of the intervention (20 minutes) and at follow-up after 3 and 12 months (20 minutes). There is minimal risk involved and the burden to participants is limited.

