## **3. STUDY DESIGN**

A randomized controlled design will be carried out, in which the effectiveness and user-friendliness of an online app-based VR self-help treatment 'ZeroPhobia: Aviophobia' and 'ZeroPhobia: Arachnophobia' will be evaluated. In this study, 96 (aviophobia) and 72 (arachnophobia) participants from the Dutch general population will be randomized in 2 separate RCTs over 2 conditions: the experimental condition (ZeroPhobia: Aviophobia or Arachnophobia) and a waitlist control condition. The duration of the intervention will be 6 weeks. Measures will be taken at baseline, directly after the intervention (6 weeks) and at 3- and 12- month follow-ups. All measures will be completed online. Subjects in the wait-list condition will receive the intervention after completion of the post-test. Randomization (block randomization with 6, 8, 10, and 12 blocks) will be performed by an independent researcher. Figure 1 presents the flow chart of the study.

[figure not shown]

Figure 1: flow chart

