## 5. TREATMENT OF SUBJECTS

### 5.1 Investigational product/treatment

ZeroPhobia is based on the principles of virtual reality exposure therapy (VRET) and Cognitive Behavioral Therapy (CBT). These therapies are currently the most researched and used treatments for anxiety disorders. ZeroPhobia is developed by Vrije Universiteit Amsterdam and In-Session. The content is developed by both, whereas In-Session alone is responsible for app-programming and VR development. ZeroPhobia has been tested by persons with aviophobia symptoms throughout the process of development. In a recent ZeroPhobia user-test, the VR environment was tested in 10 healthy participants. Results showed that the VR environment was rated as realistic and that subjects felt they were present in the environment. Among those who had symptoms of aviophobia, the level of anxiety raised with increased levels of difficulty of the VR environment. Anxiety reduced afterwards. ZeroPhobia: Arachnophobia will be tested among healthy participants soon.

Both ZeroPhobia: Aviophobia as well as ZeroPhobia: Arachnophobia are app-based interventions consisting of six modules that can be followed according to a user's own tempo and timing and without the intervention of a therapist. ZeroPhobia: Aviophobia is entirely unguided, whereas ZeroPhobia: Arachnophobia is guided. The participant will download the app on his or her smartphone. The program can be viewed from their mobile phone. Only when practicing in the VR environment (1 module) participants will put their mobile phone into the provided cardboard VR glasses to be able to experience the VR environment. Participants are allowed to keep the VR glasses after finishing the study.

The therapy consists of six consecutive modules, each taking between 5 to 20 minutes to complete:

1. Psychoeducation: Explanation of a specific phobia and ZeroPhobia
2. Facing your Fears: Setting your goals, explanation about exposure and the fear curve.

3. Exposure Therapy: Practicing in virtual reality and exposure feedback
4. Cognitive Therapy: Detecting automatic thoughts
5. Cognitive Therapy: Developing helping thoughts
6. The Next Steps.....: Facing your fears in daily life

Ad 1) **Psychoeducation**: Explanation of what a specific phobia exactly entails, how it can emerge and what the potential consequences are.

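### Section 8.3 sets the waitlist post-test at six weeks but lets faster intervention participants take it on finishing module six, so the timing of the primary contrast depends on arm and on self-chosen pace

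*Protocol*

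**What the plan says.** Section 8.3 gives a general rule for the post-test, "occurring after 6 weeks of either intervention or pause", and then an alternative trigger for one arm: "or after the completion of module six in the intervention group (for those participants who choose to work through the ZeroPhobia program faster". For the waitlist there is no alternative: "the participant will be informed that after a six week pause and the completion of a post-test assessment, they can begin the ZeroPhobia program". Pace is left to the participant: "Participants can follow the intervention at their own pace". Section 5.1 describes six modules, "each taking between 5 to 20 minutes to complete".

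Other statements about timing do not agree with each other:

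- Section 8.3, on the two arms: "Both groups will have the same duration of each section, however".
- Section 3: measures are taken "directly after the intervention (6 weeks", which joins the end of the intervention to a fixed week.
- Table 1: the post-test column is labelled as six weeks, with no exception.
- Summary: a "post-intervention assessment immediately after completion of the intervention", which ties the assessment to finishing.

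The post-test carries the FAS or FSQ. The Summary names the between-arm post-test difference in phobic anxiety as a main parameter.

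**The concern.** Randomisation makes the arms comparable at a common time after the start. Under section 8.3, the time of measurement in the intervention arm can be set by how fast a participant chooses to work, which is decided after allocation. In the waitlist arm it is fixed. The primary contrast may then compare a score at an earlier, variable time with a score at week 6, and any change over that interval is mixed with the treatment effect.

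The repeated measures ANOVA in section 10.1 takes post-test as one occasion. The main difficulty is in data collection: an early finisher's next scheduled FAS or FSQ after the post-test is at 3 months, so there is no week-6 score to analyse.

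Two other planned analyses are affected:

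- Section 10.2 compares flights taken by group with chi-square tests. A participant assessed early has had less time since the start in which to fly.
- The objectives ask whether usage intensity influences outcome. Pace is part of usage and would also determine when the outcome is measured.

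**Working it through.** **Timing rules side by side**

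| Place | Waitlist | Intervention |
|---|---|---|
| 8.3, general rule | 6 weeks | 6 weeks |
| 8.3, exception | none | completion of module six, if sooner |
| 8.3, statement on durations | same as the other arm | same as the other arm |
| 3 | 6 weeks | end of intervention, given as 6 weeks |
| Table 1 | 6 weeks | 6 weeks |
| Summary | not addressed | completion of intervention |

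The exception cannot hold together with equal durations or with Table 1. It agrees with the Summary. Section 3 is consistent with it only for participants who take the full six weeks.

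**Interval from start to scheduled post-test**

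- Waitlist: 6 × 7 = 42 days for everyone.
- Intervention: up to 42 days, with no minimum stated.
- Module content: 6 × 5 = 30 to 6 × 20 = 120 minutes in total. This excludes the recommended 10 minutes of daily VR practice from week 3. Finishing early is feasible, and the exception itself foresees it, but the documents do not say how many would.

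**Planned sample sizes, for context.** With two-sided alpha 0.05 and power 0.80, the t-test calculation gives 33.02, rounded up to 34 per arm, at d = 0.70, and 25.52, rounded up to 26, at d = 0.80. Both match section 4.3 before dropout. A common six-week post-test changes neither.

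**Possible directions of bias**

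- Less elapsed time and fewer practice days before an early post-test would make the effect look smaller.
- More time for spontaneous improvement in controls would also make it look smaller. Worsening on the waitlist would do the opposite.
- Measurement straight after the last exposure would make it look larger if fear later returned. The protocol gives no information on this.

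The sign is therefore undetermined.

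**Two-sided illustration on assumed values.** Let p be the share of the intervention arm assessed early and s the difference, in SD units, between those participants' effect at early assessment and their effect at week 6. Then average d = planned d + p × s. Neither p nor s is in the documents. Assume p = 0.10 to 0.50 and s = -0.2 to +0.2. Approximate power is Φ(d × √(n/2) − 1.96).

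| Trial (n per arm) | p | Average d | Power |
|---|---|---|---|
| Aviophobia (34) | 0 | 0.70 | 0.82 |
| | 0.10 | 0.70 ± 0.02 = 0.68 to 0.72 | 0.80 to 0.84 |
| | 0.50 | 0.70 ± 0.10 = 0.60 to 0.80 | 0.70 to 0.91 |
| Arachnophobia (26) | 0 | 0.80 | 0.82 |
| | 0.10 | 0.80 ± 0.02 = 0.78 to 0.82 | 0.80 to 0.84 |
| | 0.50 | 0.80 ± 0.10 = 0.70 to 0.90 | 0.71 to 0.90 |

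**The case against.** The best defence is that assessment at the end of treatment is a deliberate choice, with six weeks as the outer limit. The Summary supports that reading. Section 8.3 also describes module work as a weekly amount and starts VR practice at week 3, which suggests a nominal pace of about one module a week, so few may finish early. Participants who do not finish early are due at six weeks, like the controls. The flow chart cited for durations is not available here and might say more.

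What stands is that the share affected is unknown and may be small. But completing module six has no counterpart on the waitlist, so an end-of-treatment assessment in one arm has no matched control time. Keeping everyone in the intention-to-treat analysis does not align the times. Reviewing the analysis procedure before the data are analysed, as section 10.1 foresees, cannot supply a score that was not collected.

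A reader might infer more than the documents support:

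- **That the clause inflates the effect.** As shown above, extra time for controls to improve and fewer practice days both point the other way, and return of fear is not addressed. A one-sided upward bias is not established.
- **That early assessment of motivated fast finishers is a separate selection bias.** The same people are in the arm mean whenever they are assessed. Only the change in score between the two times matters.
- **That the 3- and 12-month follow-ups need a new anchor for the same reason.** Those are comparisons with baseline within the intervention arm, so the between-arm argument does not reach them.

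**Conclusion.** The concern holds as a matter of text and design. Section 8.3 contradicts itself and Table 1, and under its exception the primary outcome is measured at a time that depends on arm and on behaviour after randomisation. Only intervention participants who finish before six weeks are affected.

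The bias cannot be signed or sized from the documents. The range of d from 0.60 to 0.80 in the aviophobia trial rests wholly on the assumed 10-50% early finishers and ±0.2 SD shift. It shows what could matter and is not an estimate. At the 10% end the change in d is at most 0.02. The case for changing the plan is that the mismatch is avoidable, cannot be repaired after data collection, and affects the primary contrast in two small trials.

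**What to change.** In section 8.3, remove completion of module six as a trigger for the primary outcome. State that the FAS or FSQ post-test is sent to every participant in both arms at six weeks from the start Monday, whatever their module progress. Bring the Summary and section 3 into line with this and with Table 1, and check the flow chart. A usability survey on completion can stay as an addition. Participants may still work at their own pace.

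The cost is a few sentences and one survey trigger, with no change to sample size. The downside is that some fast finishers wait for the post-test and a few may not respond. The reminders already planned in section 8.3 would apply to them as well.
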